## Abstract

**Background:**

In previous retrospective studies, low serum progesterone level on the embryo transfer day is associated with lower clinical pregnancy and ongoing pregnancy rates. Whether adding progesterone in low serum progesterone patients can rescue the outcome, there is no sufficient evidence from randomized controlled studies.

**Methods:**

This trial is a clinical randomized controlled study (high serum progesterone vs low serum progesterone 1:1, 1:1 randomization ratio of intervention vs the control group with low serum progesterone). The eligible hormone replacement therapy—frozen embryo transfer (HRT-FET) cycles, will be recruited and randomly assigned to two parallel groups when serum progesterone is < 7.24μg/l on the day of embryo transfer for D3. The intervention group will be extrally given intramuscular progesterone 40 mg per day from D3 to 8 weeks of gestation if clinical pregnancy. The primary outcome is the ongoing pregnancy (beyond 12 weeks of gestation) rate.

**Discussion:**

The findings of this study will provide strong evidence for whether the progesterone addition from the D3 in low serum progesterone patients can improve the outcome in the HRT-FET cycle.

**Trial registration:**

ClinicalTrials.govNCT04248309. Registered on January 28, 2020

## Background

Nowadays, frozen embryo transfers(FET) becomes more and more popular in assisted reproductive technology (ART) because it can reduce the ovarian hyperstimulation syndrome (OHSS) rate in fresh cycles especially when agonist trigger in antagonist cycles and elective freezing of all embryos are used. Many centers prefer hormone replacement therapy (HRT)-FET because it can be flexible on which day the exogenous progesterone (P) is added very precisely and make embryo transfer (ET) day to be scheduled. It is essential for favoring synchrony between the embryo and the endometrium during the window of implantation. In HRT-FET using exogenous P is necessary, as a functioning corpus luteum which can produce endogenous P is not present in programed cycles. In the preimplantation period, progesterone plays an important role with 17b estradiol (E) to make the endometrium competent for embryo implantation.

HRT-FET begins with exogenous estrogens from day 2 or 3 of the patients’ menstruation to imitate the endometrium proliferative phase. Once the endometrium thickness by vaginal ultrasound reaches about 7 to 8 mm, exogenous P is supplemented to transform the endometrium to the secretory phase. The starting day of P is so-called day 0 for embryo transfer. Up to now, there is continuing debate about optimal serum estradiol and P levels in HRT-FET cycles. However, the optimal serum P level associated with the best cycle outcome is required to be established. For this reason, recently, few retrospective studies were published and concluded that serum P levels on the day of ET or the day of pregnancy test were related with ongoing pregnancy rate (OPR) [1–3]. Previous retrospective study also showed an increase in P dose after ET was insufficient to rescue pregnancy rates even in the overweight and obese patients [4].

There are several different kinds of exogenous progesterone such as intramuscular, orally, vaginally, and trans-rectum [5]. The vaginal progesterone has been most widely used in ART because of its convenience and uterine first-pass effect. Vaginal P rapidly reaches the systemic circulation, and the steady state in the serum is achieved around 48–50 h such as Utrogestan 600 mg in a day, so its serum measurement on the day of ET seems reliable. Besides, a previous study showed that increasing doses of vaginal P do not proportionally increase serum concentrations [6]. In fact, the uptake, absorption, and metabolism of progesterone can vary among individualized patients [3]. If there is an optimal serum progesterone level, this problem might be solved by increasing the P dose from the very beginning or other optimal times, but has not yet to be demonstrated. The latest prospective study concluded that low serum progesterone on the day of embryo transfer was associated with a diminished ongoing pregnancy rate in oocyte donation cycles after artificial endometrial preparation [7]. We raised the question that if progesterone added on the day of ET can improve the outcome. So, it is necessary to explore this issue in the prospective controlled study.

According to this background, we design a prospective study to explore if serum P levels on the day of ET are related with clinical pregnancy and ongoing pregnancy rate, and additional progesterone intervention is helpful to improve the outcome.

## Methods/design

### Study design

The study is designed as a randomized controlled trial. Eligible patients will be recruited in this study and checked the serum progesterone on the day of embryo transfer. According to the serum progesterone, the patients with low serum progesterone will be randomly assigned to the intervention group or the control group with a 1:1 ratio (see Fig. 1).

**Fig. 1 Fig1:**
[figure not shown]
Flowchart of the study design

### Study sites

The prospective randomized controlled study will be performed at the Reproductive Center, Sun Yat-sen Memorial Hospital of Sun Yat-sen University. It is estimated that there will be 432 HRT-FET cycles recruited to compare the ongoing pregnancy rate between the intervention group and the control group.

The Good Clinical Practice guidelines and the Declaration of Helsinki will be followed by the study. The study has been approved by the ethics committees of Sun Yat-sen Memorial Hospital of Sun Yat-sen University (2019 IRB approval no. 5).

The investigators will screen the HRT-FET patients on the day of decision with embryo transfer day. If the patients are voluntary to participate and eligible with inclusion/exclusion criteria, informed consent will be obtained from each patient before the serum progesterone test.

Reporting of the study results will follow the 2010 revised Consolidated Standards of Reporting Trials (CONSORT) statement [8].

All the main measurements and critical time points of data collection can be found in the Standard Protocol Items: Recommendations for Interventional Trials (SPIRIT) (Fig. 2).

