### Sample size calculation

A power analysis was performed according to the results from our own retrospective analysis, concluding a significant decrease in clinical pregnancy rate (CPR) when progesterone was < 7.24 μg/L (the first quartile) of 34.67% compared with ≥ 7.24 μg/L of 51.55% (*P* = 0.029).

The sample size was calculated in a two-sided test (80% statistical power, 95% confidence interval).

Low serum progesterone group: 1:1 intervention (A1) and control group (A2); high serum progesterone group: 1:1 to control group (B)

Group sample sizes are separated: 134 in group A1 and 134 in group A2 and 134 in group B. The test statistic used was the two-sided Fisher’s exact test. The significance level of the test was targeted at 0.05.

The formula is as follows:
$$ n=\frac{{\left({Z}_{1-\alpha }+{Z}_{1-\beta}\right)}^2\times \left({p}_1\left(1-{p}_1\right)+{p}_2\left(1-{p}_2\right)\right)}{{\left(\varepsilon -\delta \right)}^2} $$

After considering 5% of dropouts, 432 patients were recruited in total.

Age, BMI, endometrial thickness, serum E2, and number of transferred embryos were included in the analysis, regardless of their *P* values. Biochemical pregnancy is defined as serum HCG level ≥ 20 U/L. Clinical pregnancy is defined as observable gestation sac by transvaginal ultrasound. Ongoing pregnancy is defined as clinical pregnancy beyond gestational week 12.

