## Trial status

Ethical committee of Sun Yat-sen Memorial Hospital approval has already been obtained (2019 IRB approval no.5). The www.clinicaltrials.gov registration number is NCT04248309. The study was conceived and designed in May 2019. Enrollment began in April 2020 and was expected to end in August 2021. At the time of manuscript preparation, more than 300 subjects had been enrolled. Enrollment in this study was ongoing at the time of manuscript submission.

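### The 432 target is given both as the size of the randomised comparison and as the sum of three groups, and the stated low:high ratios conflict; counted before the progesterone test, 432 would leave the randomised arms far short of 134

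*Protocol article*

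**What the plan says.** Three places in the protocol article describe the size and make-up of the study.

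- **Study sites:** "432 HRT-FET cycles recruited to compare the ongoing pregnancy rate between the intervention group and the control group". All 432 are tied to the two-arm comparison.
- **Sample size calculation:** "Group sample sizes are separated: 134 in group A1 and 134 in group A2 and 134 in group B", followed by "After considering 5% of dropouts, 432 patients were recruited in total". Here 432 covers A1 and A2 (low progesterone, randomised) and B (high progesterone, not randomised).
- **Abstract, Methods:** "high serum progesterone vs low serum progesterone 1:1, 1:1 randomization ratio of intervention vs the control group with low serum progesterone". This sets the high and low groups equal in size.

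On sequence, the Study design section has women recruited and then tested. Study sites adds that "informed consent will be obtained from each patient before the serum progesterone test", and Selecting patients gives the same order. Women below 7.24 μg/L are randomised and all others form group B. The Sample size calculation section identifies 7.24 μg/L as the first quartile of the centre's own retrospective data ("the first quartile) of 34.67% compared with" 51.55% at or above it). Trial status reports that "more than 300 subjects had been enrolled" and that enrolment was continuing.

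**The concern.** The primary question is A1 against A2, and only women below the cutoff contribute to it. A recruitment total controls the power of that comparison only if it is counted in randomised women. The article attaches one number, 432, to two different populations and gives two different low:high ratios. A first-quartile cutoff suggests a third ratio, about one low to three high. Because women are recruited and consented before anyone knows which group they belong to, a team that counts recruited women and stops at 432 would be following the Study sites sentence as written. It could still finish with far too few randomised women. What is at stake is whether the primary comparison has roughly the planned power or about half of it.

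**Working it through.** **Inputs from the Sample size calculation section.** Rates 34.67% and 51.55% (clinical pregnancy); two-sided 0.05; 80% power; 134 per group; 5% dropout; total 432; cutoff at the first quartile. **Assumption:** the share of trial women below the cutoff. The article gives no figure for the trial population, so 25% is carried over from the retrospective data and varied.

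**1. Reproducing 134.** Difference d = 0.5155 − 0.3467 = 0.1688; mean rate 0.4311. With pooled variance under the null,

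n = [1.960 × √(2 × 0.4311 × 0.5689) + 0.842 × √(0.3467 × 0.6533 + 0.5155 × 0.4845)]² / 0.1688² = 133.9, so 134 per group. This matches the article.

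**2. Reproducing 432.** 3 × 134 = 402, and 402/0.95 = 423.2, so 424. Rounding up by group, 134/0.95 = 141.05, so 142, and 3 × 142 = 426. The stated 432 = 3 × 144 is slightly above both, and 144 × 0.95 = 136.8 covers 134. So 432 is a three-group total: 288 randomised plus 144 in B.

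**3. Ratios.**

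| Source | Low:high | Low women out of 432 | Per randomised arm |
|---|---|---|---|
| Group sizes, 134/134/134 | 2:1 | 288 | 144 |
| Abstract | 1:1 | 216 | 108 |
| First-quartile cutoff, all recruited women kept | about 1:3 | 108 | 54 |

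Only the first row is a stated set of group sizes. The other two are what the abstract's ratio and the quartile imply for a total of 432.

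**4. Yield if 432 counts women recruited before the test.** Per arm = 432 × share / 2. Power is exact, from the two binomial distributions, for 34.67% v 51.55%, before any dropout.

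| Share below cutoff | Per arm | Power, chi-square | Power, Fisher |
|---|---|---|---|
| 25% | 54 | 41% | 34% |
| 30% | 65 | 49% | 42% |
| 40% | 86 | 63% | 56% |
| 50% | 108 | 70% | 65% |

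The share needed for 134 per arm is 268/432 = 62%, or about 65% with 5% dropout (268/0.95 = 282; 282/432).

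**5. Number to test if 432 means filled groups.** Tested = randomised / share.

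| Share below cutoff | For 268 randomised | For 288 randomised |
|---|---|---|
| 25% | 1,072 | 1,152 |
| 30% | 893 | 960 |
| 40% | 670 | 720 |
| 50% | 536 | 576 |

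At 25%, 1,152 tested women include 1,152 − 288 = 864 at or above the cutoff. Taking every woman at or above the cutoff therefore cannot give a group B of 134 or 144.

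**The case against.** The best defence is that the Sample size calculation section plans filled groups: "134 in group A1 and 134 in group A2 and 134 in group B", raised to 432 for dropout. On that reading 432 counts women already placed in groups, the arms reach 134, and the Study sites sentence is only loose wording. The abstract's 1:1 may likewise be a compression of the statement that B matches one low-progesterone group. Nothing in the article says that recruitment stops at 432 consented or tested women. This stands to the extent that the shortfall is conditional. It does not make the three statements agree, and the recruit-then-test sequence does not describe filling groups to a quota.

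The 25% is also an assumption. Eligibility limits and the permitted oral dydrogesterone could make the trial population differ from the retrospective one. That stands too, hence the range, but no share near a first quartile approaches 62%.

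Three stronger readings are tempting and not supported:

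- **Less than half the planned power.** At 25% this holds for Fisher (34% of a planned 80%) but not for chi-square (41%).
- **Group B would fill early and come from a different calendar period.** No section describes a capped, first-come group B. Any such effect would touch only the non-randomised comparison with B, not A1 against A2.
- **The reported enrolment already shows a deficit.** Trial status does not say whether the 300 are consented, tested or grouped women.

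Finally, a condensed article may leave the screening number and the selection of B to the full protocol, and the flowchart is not shown. The finding therefore rests on the conflict between stated figures, not on their absence.

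**Conclusion.** The concern holds as an internal contradiction with a conditional consequence. The Study sites sentence and the abstract's ratio do not agree with the group sizes in the Sample size calculation section. That is certain from the text.

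The effect on power depends on what is counted:

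- **Counted before the progesterone test:** about 54 per arm and 34% to 41% power at a 25% low share, rising to 108 per arm and 65% to 70% even at the abstract's 1:1. All of these are below the planned 80%.
- **Counted as filled groups:** the 134 per arm is covered, but about 1,150 women must be tested at a 25% share, and most high-progesterone women must be left out of B under a rule the article does not state.

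It would go too far to say that the trial as planned is underpowered, because the article does not settle which count applies. The power figures use the plan's own clinical pregnancy rates and take the low share as the one unknown.

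**What to change.** In the abstract, Study sites and Sample size calculation:

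1. State that the primary comparison needs 268 randomised women, or 288 (144 + 144) with the dropout allowance.
2. End recruitment on the number randomised, not on 432 recruited.
3. Replace the abstract's 1:1 high:low ratio with the one that follows from the group B rule chosen below.
4. Give the expected number tested as an assumption with a range, for example about 1,150 at 25% and 960 at 30% below the cutoff, for 288 randomised.
5. Choose one rule for group B:
   - all consented women at or above the cutoff over the same accrual period, in which case 144, 432 and 2:1 no longer apply as totals (B would be about 864 at a 25% share); or
   - a capped B of 144, sampled concurrently with randomisation, in which case 432 and 2:1 stand.

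The two rules cannot be combined.

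The cost is mainly wording. The randomised target does not change. The stated screening number becomes less favourable, and the first option for B adds some data entry. As enrolment was still open when the article was submitted, the team should also establish which count its running total represents.

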**Fig. 2 Fig2:**
[figure not shown]
Standard Protocol Items: Recommendations for Interventional Trials (SPIRIT) figure

### Training of investigators

All investigators have achieved the certifications of Good Clinical Practice before the study starts. The pre-trial training of the study protocol will be conducted for all the participant investigators.

### Study population

This study will recruit the patients who are planned as HRT-FET including GnRHa downregulated plus HRT-FET cycles.

### Patient population

This study will recruit infertile patients undergoing HRT-FET cycle. All the patients will be performed a single or double embryos transfer in the cleavage or blastocyst stage. The eligibility criteria are as follows.

### Inclusion criteria

The following are the inclusion criteria:
HRT-FET cycles, including GnRHa-HRT-FET.Age < 41 years old.BMI < 30 kg/m^2^.TSH and PRL normal (0.27–4.0 mu/L for TSH and < 26 ng/mL for PRL)Endometrium thickness ≥ 8 mm on D0.Embryo transfer completed with at least 1 top-quality embryo (7–9 cell grade 1 or D5 beyond grade 3) within 2 embryos.Luteal phase support: transvaginal progesterone (Utrogestan) 600–800 mg/day with or without oral progesterone (dydrogesterone) 10 mg bid.Each patient is recruited only once.

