### Randomization and blinding

Randomization is carried out in concealed envelopes by a computer-generated randomization list generated by a research assistant who is not involved in the participant’s clinical management. Randomization will be done in a 1:1 ratio in blocks, stratified according to D3 or D5 embryo transfer. On the D3 of the HRT-FET cycle, the investigators get a concealed envelop by different blocks in sequence to obtain the randomization numbers and allocate groups for the eligible patients. Participants will be randomized into one of the two groups on the D3 when serum progesterone is less than 7.24μg/L, if the intervention group has intramuscular progesterone 40 mg per day from D3 to weeks 8 if clinical pregnancy, and if the control group has no extra intervention. The clinicians, nurses, and the participants all will not be blinded to the treatment allocation. The statistician is blinded to the group allocation.

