### Procedures

#### Study protocol (endometrial preparation)

All the included patients receive HRT for endometrial preparation. Treatment starts on day 2 or day 3 of menstruation with oral estradiol valerate administration (Progynova®, Bayer Guangzhou, China)—constant dose 4–8 mg/d or step-up increasing dose protocols, and the endometrium thickness will either be checked once during the first 5–7 days. The estradiol dose will be adjusted accordingly. After about 10–14 days of estrogens, a transvaginal ultrasound will be performed to measure the endometrial thickness and to confirm a triple layer pattern. Patients are considered ready for ET once endometrial thickness reaches 8 mm, and quiescent ovaries are detected by ultrasound, serum E2 > 150 pg/mL, and the serum P level < 2 ng/mL. Transvaginal P (Utrogestan® Besins, France) will be administered 3 or 5 days before embryo transfer at a dose of 200 mg tid or 400 mg bid Utrogestan vaginally. Transvaginal progesterone will be started 3 days before embryo transfer for patients who will have day 3 embryo transferred or 5 days before embryo transfer for those who will have day 5 embryo transferred. Serum progesterone will be tested on the morning of D3 (after 3 days of progesterone addition) after the first dose of progesterone, approximately 2 h beforehand. In case of pregnancy, HRT was maintained until gestational weeks 10. The estrogen would be gradually decreased with dosage after gestation at 8 weeks. The progesterone dosage would be not changed.

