#### Selecting patients

On the first day of progesterone supplementation (day 0), eligible patients are selected for this study. After checking all the inclusion and exclusion criteria, patients will be informed about the nature of the study, read the informed consent (IC) form, and decide if they wish to participate. After signing the IC form, a blood test of progesterone is performed on day 3. According to the serum progesterone level on day 3, if P is ≥ 7.24 ng/mL, continue with the transvaginal progesterone until the pregnancy test on days 14–16. If P < 7.24 ng/mL, according to the randomization numbers, the patient is randomized to either non-intervention control group or intervention group with intramuscular progesterone 40 mg until the pregnancy test on days 16–17. This protocol will continue until gestation week 8 and withdraw the intramuscular progesterone.

The included patient should test the serum progesterone level on D3 no matter which day the embryo transfer will be performed. According to the progesterone level, there are two groups:
Group A: serum progesterone < 7.24μg/L, followed by randomized:
A1: plus additional treatment (intramuscular progesterone 40 mg per day from D3)A2: without additional treatmentGroup B: serum progesterone ≥ 7.24μg/L, without additional treatment

Samples will be tested by the Beckman chemiluminescence method (Beckman DXI800, Roche, USA). The intra- and inter-assay variation coefficients for the P determinations were 6.11–11.19% and 7.51–9.57%, respectively, for *P* values between 1.26 and 22.61 ng/mL. The intra- and inter-assay variation coefficients for the E2 determinations were 2.4–10.5% and 2.4–9%, respectively, with a measurement range of 50–120 pg/mL.

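### Completed transfer with a top-quality embryo is an inclusion criterion, but women are randomised open-label on D3, two days before transfer in the D5 stratum

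*Protocol article*

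**What the plan says.** Five statements in the protocol article bear on this point.

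- **Inclusion criteria:** "Embryo transfer completed with at least 1 top-quality embryo", out of at most two embryos.
- **Selecting patients, time of the eligibility check:** "On the first day of progesterone supplementation (day 0), eligible patients are selected for this study". All inclusion and exclusion criteria are checked at that time, before consent and before the progesterone test.
- **Selecting patients, time of the test:** "The included patient should test the serum progesterone level on D3 no matter which day the embryo transfer will be performed".
- **Randomization and blinding:** "Participants will be randomized into one of the two groups on the D3 when serum progesterone is less than" 7.24 μg/L, with stratification by D3 or D5 transfer. The same section adds: "The clinicians, nurses, and the participants all will not be blinded to the treatment allocation".
- **Study protocol (endometrial preparation):** vaginal progesterone starts 3 days before transfer for day 3 embryos, "or 5 days before embryo transfer for those who will have day 5 embryo transferred".

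**The concern.** An inclusion criterion should be decidable before the allocation is known. This one depends on an event that has not happened for any woman at the day-0 check, and has not happened at randomisation for any woman in the D5 stratum. In that stratum it is settled up to two days after allocation and the start of study treatment, by staff and participants who know the arm.

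If the criterion were then used to decide who belongs in the trial, a randomised woman without a qualifying transfer would leave the denominator of the primary endpoint instead of counting as having no ongoing pregnancy. If that happened more often in one arm, the arms compared would no longer be the arms that were randomised. The arm losing more non-pregnant women would show the higher rate, so the bias could run in either direction, and a larger sample would not remove it.

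**Working it through.** **1. Timeline, from the sections cited above**

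| Event | D3-transfer stratum | D5-transfer stratum |
|---|---|---|
| Eligibility check | Day 0 | Day 0 |
| Progesterone test and randomisation | D3 | D3 |
| Transfer | D3 (order relative to randomisation not stated) | D5 |
| Gap from randomisation to transfer | Same day | 5 − 3 = 2 days |

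Read literally, nobody meets the criterion on day 0. For the D5 stratum it is certain that it is decided after randomisation. For the D3 stratum the article leaves this open.

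**2. The plan's own sample size**

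Inputs (Sample size calculation): clinical pregnancy rates 34.67% and 51.55%, two-sided 5% level, 80% power. Difference: 51.55 − 34.67 = 16.88 points. Mean rate: 43.11%.

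n = [1.96·√(2 × 0.4311 × 0.5689) + 0.8416·√(0.3467 × 0.6533 + 0.5155 × 0.4845)]² / 0.1688²

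This gives 134 per group, as stated. The recruitment total of 432 over three groups is 432/3 = 144 per group. Neither figure changes through this point; they serve only as a scale.

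**3. How many women could be affected**

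The article gives neither the D5 share nor the proportion of D5 women without a qualifying transfer. Assumed ranges: share s = 30% to 70%, proportion f = 2% to 15%. Women lost per arm = 144 × s × f.

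- Low end: 144 × 0.30 × 0.02 = 0.9
- High end: 144 × 0.70 × 0.15 = 15.1

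After a further 5% dropout, 136.0 and 122.4 women per arm remain. On the same normal approximation, power is 0.81 and 0.76 respectively.

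**4. Size of the bias if such women were dropped**

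Assume no true effect, the same ongoing pregnancy rate p in both arms when all randomised women are counted, and no ongoing pregnancy in any dropped woman. With proportions a and b of D5 women dropped in the two arms, the spurious difference is

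p/(1 − s·a) − p/(1 − s·b).

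| p | s | a vs b | Calculation | Difference (points) |
|---|---|---|---|---|
| 35% | 30% | 10% vs 2% | 0.35/0.970 − 0.35/0.994 | 0.87 |
| 35% | 50% | 10% vs 2% | 0.35/0.950 − 0.35/0.990 | 1.49 |
| 45% | 70% | 10% vs 2% | 0.45/0.930 − 0.45/0.986 | 2.75 |
| any | any | equal | both terms identical | 0 |

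The assumption that dropped women are not pregnant fits a transfer that did not take place. It fits less well for a transfer done without a top-quality embryo, where a pregnancy is possible.

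**The case against.** **No exclusion rule is written.** The Withdrawal criteria cover voluntary withdrawal only, the Statistical analysis section defines no completed-transfer set, and the 5% allowance is for dropouts, not for ineligible women. A reader might infer that the trial does drop women after randomisation and that its comparison is therefore broken. The documents do not support that. They contain a criterion which would have this effect if followed to the letter. This objection stands and limits the point.

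**The criterion may simply mean a planned transfer.** The Study population and Patient population sections speak of planned cycles and of transfers still to come. Because the embryos are frozen, their existence and the intended stage are known before day 0. That may well be the intention, but the text says *completed*. If *planned* was meant, the wording needs correcting.

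**Analysis sets belong in the statistical analysis plan.** Agreed: their absence from a journal article is not criticised here. The point is a stated criterion that does not fit the stated times of eligibility checking and randomisation.

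**A larger bias can be constructed.** Take 134 per arm, 47 ongoing pregnancies in each (35.1%), and drop non-pregnant women from one arm only. Dropping 8 gives 47/126 = 37.3%, a shift of 2.2 points; dropping 13 gives 47/121 = 38.8%, a shift of 3.8 points. A reader might take these as the expected size. They rest on wholly one-sided dropping: if half the arm were D5 transfers, 13 of 67 is about 19% of D5 women in one arm against none in the other. Nothing in the article suggests that.

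**The mechanism is conjecture.** The Discussion names cancelling or delaying the transfer after a low value as open questions, so decisions that differ by arm are conceivable with unblinded staff. No trial procedure calls for them.

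**Conclusion.** The wording of the criterion contradicts the trial's own timeline. The conflict with the day-0 check concerns every woman. The conflict with randomisation is certain for the D5 stratum and undetermined for D3 transfers. Applied literally, the criterion would make some D5-stratum women ineligible once their arm is known.

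Whether anyone is removed, and how often a qualifying transfer fails to take place, cannot be learned from the article. On the assumptions shown, the bias is zero with equal dropping and about 1 to 3 points with 10% versus 2% dropping, which is modest beside the planning difference of 16.9 points. That planning difference is in clinical pregnancy rate, so it is only a yardstick for the ongoing pregnancy endpoint. The point should be fixed because the remedy is cheap and protects the primary comparison; it does not show that the comparison is already compromised.

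**What to change.** 1. **Women still to be enrolled:** reword the criterion to a planned transfer of one or two embryos, at least one of top quality, as known before randomisation, and record this on the case report form before the envelope is opened.
2. **All women, including those already randomised:** state that the completed-transfer criterion is not used to exclude anyone after randomisation. Analyse every randomised low-progesterone woman in her allocated arm, with no transfer counted as no ongoing pregnancy. A woman whose transfer was done without a top-quality embryo counts with her observed outcome.
3. **Sensitivity analysis:** keep the completed-transfer set, and report by arm how many women are left out of it and why.

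Cost: a short amendment, one data field and a slight dilution of the ongoing pregnancy rate. According to Trial status, more than 300 subjects had been enrolled when the article was prepared, so the new entry wording cannot reach them. For them the protection comes from item 2, which should be settled before outcomes are compared. Outcomes should be obtained for any randomised woman already set aside under the criterion.
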